#### Short form eating disorder examination questionnaire adapted for children (ChEDE-Q8)

The Child Eating Disorder Examination-Questionnaire (ChEDE-Q) is a self-report version of the Child Eating Disorder Examination (ChEDE). The English version of the ChEDE-Q8 has been derived from the German version of the ChEDE-Q8 [40] and the English version of the ChEDE-Q [41]. The ChEDE-Q8 is an 8-item self-report measure that evaluates four areas of eating disorder psychopathology: restraint, eating concern, shape concern, and weight concern. ChEDE-Q8 scores range from 0 (absence of the feature) to 6 (feature present every day or to an extreme degree). Global mean scores will be used, with higher scores indicating higher levels of eating disorder psychopathology. The ChEDE-Q8 was validated for children ages 7 and above and has been shown to have strict measurement invariance, internal consistency, and convergent as well as factorial validity [40].

#### Child eating Behavior Questionnaire (CEBQ)

The CEBQ [42], which is to be completed by the parent of a child under assessment, is a 35-item measure used to evaluate cognitions, emotions, and behaviors associated with disordered eating. Eight aspects of eating behavior are assessed: food responsiveness, emotional over- and undereating, enjoyment of food, desire to drink, satiety responsiveness, slowness in eating, and food fussiness. The CEBQ is rated on a 5-point Likert scale with scores ranging from 1 (never) to 5 (always). The eight subscale scores and global mean score will be used for analysis, with higher scores indicating a greater level of disordered eating. The CEBQ has been shown to have high test-retest reliability and is a valid method of assessing obesogenic eating behaviors [42, 43].

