In addition to clinical trial evidence, there are also neurobiological studies that support the use of stimulants as a treatment for LOC-E [22, 23]. For example, explanatory models for ADHD suggest that reduced dopamine neuronal tone affects executive functioning and reward processing [24]. Similarly, disordered eating, such as binge eating has been associated with lower dopamine (and norepinephrine) metabolite levels in the cerebrospinal fluid [25, 26]. In sum, for ADHD and eating disorders, there is evidence of altered dopaminergic tone, presumably *lower* intrasynaptic dopamine, and since stimulant medications *increase* intrasynaptic dopamine and norepinephrine levels in striatal and cortical brain regions, a plausible explanatory model supports the use of stimulant medication for LOC-E.

As further support for exploring the effect of stimulants on LOC-E in youth, retrospective and cross-sectional data suggests that children with ADHD who had been treated with stimulants had less odds of obesity compared to those who were not medicated [27]. Importantly, the research does not elucidate whether stimulants were associated with lower obesity rates because they lessened symptoms of LOC-E, or alternatively, whether a different mechanism mediated the apparent effect on obesity (e.g., appetite suppression independent of effect on disordered eating).

In sum, though stimulants warrant investigation as a treatment for LOC-E in youth, no studies have prospectively examined the effect of stimulants on this form of disordered eating. To gather pilot data, we aim to measure prospective, observational outcomes in a clinical setting to examine the effect of stimulant initiation on LOC-E in children with comorbid ADHD and LOC-E. We will also collect exploratory secondary outcomes to measure eating-related cognitions, emotions and behaviors, ADHD symptom severity, parental LOC-E, impulsivity and reward sensitivity, and anxiety/mood symptoms. Given the observational design, we will not generate a priori hypotheses.

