### Secondary outcomes

The secondary outcomes of this study include disordered eating cognitions, emotions, and behaviors (measured using the ChEDE-Q8 and CEBQ), ADHD symptom severity (measured using the VADPRS), impulsivity and reward sensitivity (measured using the BIS/BAS), and anxiety/mood severity (measured using the RCADS-25).

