### Data analytic plan

Within-patient standardized effect size information (i.e., Cohen’s d and 95% confidence intervals) from baseline to 3-month follow-up will be calculated for LOC-E episodes and all secondary outcomes. Clinical outcome data will be analysed for all youth who remain on a stimulant for the 3-month duration. Descriptive statistics (e.g., means and standard deviations) will be used to report demographic information, medication doses, adverse events, and frequency of medication discontinuation. If available, reasons for medication discontinuation and loss to follow-up will be documented. Given the case series design, there will be no a priori power analysis.

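### The CEBQ scoring sentence gives eight partly opposing subscales, and their global mean, one direction of disorder and states no reverse-keying

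*Protocol article*

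**What the plan says.** The CEBQ section under Measures lists the eight aspects of eating behavior as "food responsiveness, emotional over- and undereating, enjoyment of food, desire to drink, satiety responsiveness, slowness in eating, and food fussiness". On response format it says "The CEBQ is rated on a 5-point Likert scale with scores ranging from 1 (never) to 5 (always"), and it mentions no reversal of any item or subscale. Scoring is then fixed in one sentence: "The eight subscale scores and global mean score will be used for analysis, with higher scores indicating a greater level of disordered eating". The section closes by saying that the questionnaire "is a valid method of assessing obesogenic eating behaviors".

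Secondary outcomes uses the instrument for "disordered eating cognitions, emotions, and behaviors (measured using the ChEDE-Q8 and CEBQ"). The Data analytic plan says that within-patient Cohen's d with a 95% confidence interval "from baseline to 3-month follow-up will be calculated for LOC-E episodes and all secondary outcomes". The CEBQ therefore yields nine planned effect sizes: eight subscales and one global mean.

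**The concern.** A single direction can hold for all eight subscales only if they all point the same way or if some are reversed before scoring. By their names they do not all point the same way, and no reversal is stated.

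Two things follow for a reader who applies the sentence as written. First, a child who becomes more responsive to satiety after starting a stimulant is reported as more disordered on that subscale, although the same section presents the instrument as measuring obesogenic eating. Second, the global mean adds changes of opposite meaning, so its Cohen's d has no clear interpretation: a value near zero could mean that nothing changed or that several subscales changed in opposite directions. The Discussion offers these secondary outcomes as pilot data for later work on mechanisms, so a mislabelled or uninterpretable effect size could be carried forward.

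**Working it through.** The plan gives no figure for the CEBQ to reproduce. The check has three parts.

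**1. Direction, from the text alone.** Emotional overeating and emotional undereating are opposites by name. Food responsiveness and enjoyment of food describe a pull towards food; satiety responsiveness and slowness in eating describe the reverse. With higher scores read as more disordered and the construct described as obesogenic eating, the direction fits the first group and fails at least for satiety responsiveness and slowness. The BIS/BAS section shows the alternative in the same article: it keeps the four subscale totals separate, reads each as more of its own motivational system, and forms no overall score.

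**2. Arithmetic of the global mean.** Assumptions, none of them in the article: the mean weights eight subscales equally, each of *a* approach subscales falls by 0.5 point, each of *b* avoidance subscales rises by *r* × 0.5, and the rest do not move.

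- As written: change = (-0.5*a* + 0.5*rb*)/8
- Avoidance subscales reverse-keyed: change = (-0.5*a* - 0.5*rb*)/8
- The as-written change is zero when *r* = *a*/*b* and positive above that.

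The grouping is read from the subscale names, so four versions are shown. Each cell gives as written / reverse-keyed.

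| Grouping | r = 0 | r = 0.5 | r = 1 | r = 1.5 |
|---|---|---|---|---|
| 3 approach, 2 avoidance (satiety, slowness) | -0.188 / -0.188 | -0.125 / -0.250 | -0.063 / -0.313 | 0 / -0.375 |
| 3 and 3 (adding emotional undereating) | -0.188 / -0.188 | -0.094 / -0.281 | 0 / -0.375 | +0.094 / -0.469 |
| 3 and 4 (adding fussiness) | -0.188 / -0.188 | -0.063 / -0.313 | +0.063 / -0.438 | +0.188 / -0.563 |
| 4 and 4 (also counting desire to drink as approach) | -0.250 / -0.250 | -0.125 / -0.375 | 0 / -0.500 | +0.125 / -0.625 |

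For the first row at *r* = 0.5: (-1.5 + 0.5)/8 = -0.125, against (-1.5 - 0.5)/8 = -0.25.

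**3. Carry-over to Cohen's d.** Here d is the mean change divided by the SD of the change, so a zero or a wrong sign in the table carries over directly. The degree of attenuation does not, because it also depends on how the subscale changes correlate. For the 4-and-4 case, assume a change SD of 0.7 per subscale and a shared appetite factor giving correlation ρ within each group and -ρ between groups:

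- SD as written = 0.7 × √((1 - ρ)/8)
- SD reverse-keyed = 0.7 × √((1 - ρ)/8 + ρ)

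| ρ | r | d as written | d reverse-keyed |
|---|---|---|---|
| 0 | 0.5 | -0.125/0.247 = -0.51 | -0.375/0.247 = -1.52 |
| 0 | 1 | 0 | -0.500/0.247 = -2.02 |
| 0.3 | 0.5 | -0.125/0.207 = -0.60 | -0.375/0.436 = -0.86 |
| 0.3 | 1 | 0 | -0.500/0.436 = -1.15 |
| 0.5 | 0.5 | -0.125/0.175 = -0.71 | -0.375/0.525 = -0.71 |
| 0.5 | 1 | 0 | -0.500/0.525 = -0.95 |

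In raw points the as-written change is always less negative than the reverse-keyed one once avoidance rises. In d units the gap ranges from large to nil, as the ρ = 0.5, *r* = 0.5 row shows.

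**The case against.** The strongest reply is that this is a condensed article and that reverse-keying may be set out in a fuller document; with it, the direction sentence could be true. It is right that unsigned averaging is an inference from silence. The point stands in that form because the article does not leave direction open: it states one direction for every subscale and for the mean, and says nothing that would make it true.

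Second, the eight subscales are also analysed, so every shift in the illustration would appear in its own effect size. This stands. A reader might infer that the appetite signal is lost; it is not. What remains is that the subscale results carry the wrong label for at least satiety responsiveness, and that the ninth figure is hard to read.

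Third, the construct is named disordered eating, not overeating. Emotional undereating and food fussiness can reasonably count as disordered in that wider sense, so a higher score on those two is not clearly mislabelled. This also stands, and it limits the direction error mainly to satiety responsiveness and slowness. It does not rescue the mean, which would then combine different problems pointing in different directions.

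Fourth, a reader might infer that the Background requires appetite effects to be separated from change in loss-of-control eating. It does not. It says that earlier obesity research leaves the mechanism open and gives "appetite suppression independent of effect on disordered eating" as an example. That makes the opposing pattern plausible here, but it is not a stated aim of the study or of the CEBQ.

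**Conclusion.** The point holds as a scoring rule that misleads if followed as written. Its direction is wrong for at least satiety responsiveness and slowness in eating unless those are reverse-keyed, and the global mean has no clear meaning across opposing traits.

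It would go too far to say that an appetite effect cancels out. Cancellation is exact only when the summed falls and rises balance; otherwise the global change is attenuated or reversed. In the illustration the as-written change runs from -0.25 to +0.188 point across groupings and *r* from 0 to 1.5. These sizes rest on assumed shifts, SDs, correlations and equal subscale weights. The article does not say whether the global mean averages the 35 items or the eight subscales, although it does say so for the LOCES.

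The reach is limited. One secondary outcome, which the Background calls exploratory, is affected. The primary outcome, episode frequency from the ChEDE, is not. The article sets no a priori hypotheses or power analysis, and it ties no decision to the CEBQ mean. The correction should be made because it is simple and prevents a misread result.

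**What to change.** In the CEBQ section, delete the global mean and the statement that higher scores always indicate more disordered eating. Keep the eight subscales, each with its own effect size, and state for each what a higher score means, as the BIS/BAS section does for its subscales. If any subscale is in fact reverse-keyed, name it.

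If a summary is wanted, report separate food-approach and food-avoidance composites in place of one mean across all eight. Justify their membership from the instrument, in particular for food fussiness and desire to drink, which cannot be placed from their names alone.

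The cost is an edit to the scoring text. The questionnaire, visits and data collected stay the same.

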#### Loss of Control Over Eating Scale (LOCES)

The LOCES [44], which is to be completed by parents in relation to their own eating psychopathology, is a 24-item self-report measure used to examine three aspects of LOC-E: behavioral, cognitive/dissociative, and positive/euphoric. The LOCES consists of three subscales based on the three aspects of LOC-E, with scores ranging from 1 (never) to 5 (always) on a 5-point Likert scale. The global mean score calculated from the average of each subscale will be used, with higher scores indicating greater levels of LOC-E. The LOCES has been shown to have high internal consistency, convergent and discriminant validity, and test-retest reliability [44].

#### Parent-report behavioral inhibition System/Behavioral activation system scales (BIS/BAS)

The BIS/BAS [45] is a 20-item parent-report measure (examining their child’s behavior), adapted from the original self-report BIS/BAS scales [46], which examines two motivational systems through responses to reward and punishment. The BIS/BAS contains four subscales: the inhibition system (BIS), reward responsiveness (BAS), drive (BAS), and fun seeking (BAS). Impulsivity has been found to be positively correlated with BAS-drive and BAS-fun seeking, and negatively correlated with BIS [47], therefore, the BIS/BAS can be used as a proxy for impulsivity in youth. Seven questions related to sensitivity to punishment are used to assess the BIS, and thirteen questions related to sensitivity to reward to assess the BAS; scores range from 1 (not true at all) to 4 (all true) on a 4-point Likert scale. The total separate scores of the four subscales will be used, with higher scores indicating greater levels of sensitivity in the associated motivational system. The parent-report BIS-BAS is a reliable and valid tool for examining punishment and reward sensitivity in children [45].

#### Revised child anxiety and Depression Scale – Short Version (RCADS-25)

The RCADS-25 [48] is a 25-item self-report measure, adapted from the original 47-item RCADS [49, 50], used to assess depression and anxiety symptoms in children. The RCADS-25 contains 10 questions based on major depressive disorder, and 15 questions based on five DSM-IV anxiety domains: separation anxiety disorder, generalized anxiety disorder, panic disorder, social phobia, and obsessive-compulsive disorder. RCADS-25 scores range from 0 (never) to 3 (always) on a 4-point Likert scale. Global anxiety and depression scores will be used separately, with higher scores on each scale indicating greater levels of anxiety and depression. The RCADS-25 is a reliable clinical tool and has been shown to have discriminant, convergent, and divergent validity [51].

### Primary outcome

LOC-E episode frequency in the last 3-months is the primary outcome of this study, as measured by the ChEDE.

### Secondary outcomes

The secondary outcomes of this study include disordered eating cognitions, emotions, and behaviors (measured using the ChEDE-Q8 and CEBQ), ADHD symptom severity (measured using the VADPRS), impulsivity and reward sensitivity (measured using the BIS/BAS), and anxiety/mood severity (measured using the RCADS-25).

### Procedure

Clinicians at the ADHD clinic will routinely pre-screen for LOC-E, using the CBBEQ [29], as part of their standard clinical assessment (see Fig. 1 for schedule of assessments). The clinic’s standard ADHD diagnostic assessment includes a psychiatric history by an ADHD expert (JS) and cognitive data using a validated Continuous Performance Test (CPT). Patients who are diagnosed with ADHD and pre-screen positive for LOC-E (score of 8 or above on the CBBEQ), and who receive a recommendation to start a stimulant medication and intend to initiate the stimulant, will be invited to the consent and screening visit. Pre-screening data collection is standard practice at the clinic (i.e., relevant personal health information and scale-based outcomes) and will not be recorded for the study as consent will not have been obtained. However, clinic staff will record the following non-personal health information that can be used in a participant flow diagram for study purposes: (a) number of positive and negative pre-screens, and (b) number of patients who are interested or not interested in being contacted by a research staff to learn more about the study.

Parents and children who are interested in participating will meet with a research assistant over Zoom for Healthcare to review the consent form and undergo a more detailed screening visit to establish eligibility. During the screening visit a trained research assistant will use the diagnostic version of the ChEDE to confirm the LOC-E inclusion criteria are met. If the LOC-E diagnosis is confirmed and no exclusion criteria are met, the child’s parent will be instructed to contact the research assistant approximately 2 weeks prior to stimulant initiation (which will occur naturalistically in the child’s physician’s office outside of the study context). At that time, participants will meet with a research assistant again to obtain baseline measurements (i.e., prior to stimulant initiation) and demographic information (age, sex, previous and current psychological and pharmacological treatments, and parent reported comorbid diagnoses of physical and psychiatric conditions). Outcome measurements will be gathered again at 3-months after initiating the stimulant, as will information about the stimulant treatment (i.e., type, dose, adherence, and adverse events [adapted from the Pittsburgh Side-Effects Rating Scale]) [52]. Participants will be paid $25 per visit after the final study visit.

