### Participants

We will collect data on forty 8–13-year-old youth and their parents. The study will use a prospective cohort sample from the Atlantic ADHD Centre in Dartmouth, Nova Scotia. To be eligible for inclusion, youth must (A) meet the diagnostic criteria for ADHD, and (B) have experienced at least 3 episodes of LOC-E during the past 3 months^1^, accompanied by some degree of distress and 2 of the 5 behavioral symptoms associated with LOC-E. Inherent to the definition of LOC-E, consumption of an abnormally large amount of food will not be required. Further details related to the diagnostic assessment for ADHD and LOC-E are provided in later sections. Participants will be excluded if they are (a) currently receiving psychotherapy treatments for ADHD, eating disorders, or obesity, and/or (b) undergoing concurrent medication changes that could affect ADHD or eating related symptoms (as determined by psychiatrist and principal investigator [[name]]). Participants must also have sufficient language skills and a general practitioner to initiate the stimulant and monitor adverse events.

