### Measures

The following outcome measures will be collected at various time points including the pre-screening visit, screening visit, baseline, and 3-month follow-up. Figure 1 illustrates an overview of these study visits.

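### A single adverse-event collection at 3 months, with reasons for stopping taken only where available, risks under-recording early reactions and leaving stops unexplained

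*Protocol article*

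**What the plan says.** The Measures section lists the study's time points as "various time points including the pre-screening visit, screening visit, baseline, and 3-month follow-up". The Procedure section adds that "Outcome measurements will be gathered again at 3-months after initiating the stimulant, as will information about the stimulant treatment", and spells the treatment information out as "type, dose, adherence, and adverse events [adapted from the Pittsburgh Side-Effects Rating Scale". Type, dose, adherence and adverse events are thus all tied to the one follow-up visit.

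Stimulant initiation is placed in routine care, "which will occur naturalistically in the child’s physician’s office outside of the study context". Under Participants, each child must have "a general practitioner to initiate the stimulant and monitor adverse events". The article describes no step that passes the practitioner's observations to the study team.

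The Data analytic plan promises descriptive reporting of adverse events and of how often medication was stopped. On why it was stopped, it says "If available, reasons for medication discontinuation and loss to follow-up will be documented". It also states "Clinical outcome data will be analysed for all youth who remain on a stimulant for the 3-month duration". That sentence concerns clinical outcomes; the article does not say which children form the denominator for adverse events.

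**The concern.** A reaction that makes a child stop or change product soon after starting is likely to have resolved by month 3. On the stated schedule the study first asks about it then. A child who stops in week 2 and is seen at about week 13 is asked some 11 weeks later, and a family lost to follow-up is not asked at all. The Discussion itself concedes recall bias, and points to the children's age.

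A child who changes product because of intolerance is still taking a stimulant, so that intolerance need not appear in the count of discontinuations. No stated item asks about an earlier product. The person charged with watching for adverse events works outside the study.

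The article presents the study as the first prospective look at stimulants for loss of control eating in youth, and as pilot data for later trials. Planners of those trials will want to know how many children could not continue, and why. An analysis plan cannot recover events or reasons that were never collected.

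**Working it through.** **Nothing to reproduce.** The article gives no adverse-event rate, no discontinuation rate and no power calculation. The check is a reading of the text, followed by an illustration on assumed values.

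**Reading.**

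- *Timing.* The four named time points are pre-screening, screening, baseline and 3 months. The first three precede treatment, so one named point remains for adverse events.
- *Look-back.* The article says the side-effect items are adapted from a published scale. It gives neither the recall period nor a rule for a stimulant taken earlier.
- *Who is asked.* No sentence excludes children who stopped, and none says that they are to be asked.
- *Reasons.* The conditional wording covers reasons for discontinuation and loss to follow-up. It does not cover adverse events or the count of stops.

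**Illustration.** N = 40 comes from Participants ("We will collect data on forty 8–13-year-old youth and their parents"). All other values are assumptions:

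- d = share of children who stop
- p = share of continuers with an adverse event
- q = share of stoppers with an adverse event
- m = share of stoppers whose events are not captured

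Formulas:

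- True proportion: T = (1 − d)p + dq
- Observed, all 40 kept in the denominator: A = (1 − d)p + dq(1 − m)
- Observed, unreached stoppers dropped: B = A / [(1 − d) + d(1 − m)]

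With p = 0.30 and q = 0.80:

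| d | T | m | A | B |
|---|---|---|---|---|
| 0.10 (4 children) | 0.27 + 0.08 = 35% | 0 | 35% | 35% |
| | | 0.5 | 0.27 + 0.04 = 31% | 0.31/0.95 = 32.6% |
| | | 1 | 27% | 0.27/0.90 = 30% |
| 0.20 (8 children) | 0.24 + 0.16 = 40% | 0 | 40% | 40% |
| | | 0.5 | 0.24 + 0.08 = 32% | 0.32/0.90 = 35.6% |
| | | 1 | 24% | 0.24/0.80 = 30% |

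Over d = 5 to 30%, p = 30 or 50%, q = 50 to 100% and m = 0 to 1, the understatement runs from 0 to 30 points under A and from 0 to 21 points under B. The upper ends arise at d = 0.30, p = 0.30, q = 1, m = 1: T = 0.21 + 0.30 = 51%, A = 21%, B = 0.21/0.70 = 30%.

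**Direction.** T − A = dqm, which is never negative. B lies below T only when q exceeds p. It equals T when q = p, and would lie above T if stoppers had fewer events than continuers. Downward bias under B therefore assumes that adverse events are commoner in those who stop.

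**Granularity.** One child in 40 is 2.5 points, so two or three unexplained stops amount to 5 to 7.5 points of the cohort.

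**The case against.** The strongest reply is that the article is a condensed account. The adapted side-effect form is not shown, and it may already ask about the whole period since initiation, product by product. The schedule figure is not shown either, and the list of time points is introduced in a way that need not be exhaustive. This stands: the absence of interim contact is a statement about the text available, and the loss of early events is a risk and not an established fact.

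A reader might infer more: that early reactions are mostly lost, and that tolerability will look better than it was. The documents do not support this. The restriction to children still on a stimulant is written for clinical outcomes. The promise to report stops implies that stoppers are identified, and nothing bars them from the 3-month questions. Nor does anything confine those questions to the product then in use.

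A reader might also infer that switches bias the discontinuation frequency downward. They do not: a child who changes product has not stopped stimulants, and the study treats stimulants as a class. Intolerance of the first product and discontinuation are two quantities, and both are worth reporting.

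It is also fair to say that some reasons cannot be obtained from families who cannot be reached, that recall bias is already acknowledged, and that tolerability is neither a primary nor a secondary outcome.

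What survives is narrower. The text fixes one retrospective collection, does not commit to asking every initiator about the whole period, and makes reasons for stopping conditional on availability.

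**Conclusion.** The point holds as a risk of under-recording early, resolved or pre-switch reactions, and of leaving stops unexplained. Its size cannot be determined, because it depends on the share of stoppers' events that are missed, and the article gives no information on that share. It is zero if every stopper is seen and recall is complete; the text secures neither condition. The percentages under working show scale under assumed rates and are not estimates for this study. The primary outcome is untouched, and the affected results are descriptive. The change is worth making because it is cheap and because early events become harder to recover as time passes.

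**What to change.** 1. At the existing 3-month visit, put the side-effect questions to every child who took at least one dose, including those who stopped. Ask about any time since the first dose, separately for each stimulant taken.
2. Seek the reason for each stop or switch as a standard item. Report switches for intolerance separately from discontinuation.
3. At baseline, ask parents to notify the research assistant when a stimulant is stopped or changed, so that the side-effect scale and the reason can be taken by phone then. Parents are already asked to make contact before initiation, so this extends an existing arrangement.
4. State that adverse events are reported over all initiators, and give the number who could not be reached.

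The cost is a few more questions at a visit already planned and a short call for the minority who stop or switch. Recall of early events will still be imperfect for families who do not call, and the reported adverse-event rate may be less favourable.

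### The side-effects rating is described only at 3 months and no pre-stimulant rating is named, so the reported adverse events may include complaints the child already had

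*Protocol article*

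**What the plan says.** The Procedure section of the protocol article describes two study visits at which measures are compared. At the first, before treatment, "participants will meet with a research assistant again to obtain baseline measurements (i.e., prior to stimulant initiation) and demographic information". The demographic items are then listed: "age, sex, previous and current psychological and pharmacological treatments, and parent reported comorbid diagnoses of physical and psychiatric conditions". No side-effects rating is among them.

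The next sentence covers the second visit: "Outcome measurements will be gathered again at 3-months after initiating the stimulant, as will information about the stimulant treatment". Adverse events belong to that treatment information ("as will information about the stimulant treatment (i.e., type, dose, adherence, and adverse events"), and the instrument is given as "adherence, and adverse events [adapted from the Pittsburgh Side-Effects Rating Scale". The wording of the adapted items and their recall period are not given.

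The Data analytic plan says "Descriptive statistics (e.g., means and standard deviations) will be used to report demographic information, medication doses, adverse events, and frequency of medication discontinuation". The effect sizes from baseline to 3 months cover LOC-E episodes and the secondary outcomes. The Secondary outcomes section does not list adverse events, so no change from baseline is planned for them. The side-effects scale has no entry under Measures and does not appear in the legend to Fig. 1.

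**The concern.** Stimulant type, dose and adherence cannot be recorded before treatment, but the complaints on a side-effects scale can. Children with ADHD and disordered eating, some of them anxious or low in mood, may well have some of these complaints before the first dose. A single rating after treatment cannot tell a new or worsened complaint from one that was already there.

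In a controlled trial the comparison arm would supply a background rate. This is a single-group case series, and its Discussion accepts that time effects cannot be controlled. The child's own state before treatment is therefore the only comparator available, and no rating of it on this scale is described. At stake is how the adverse-event summary can be read in what the Discussion calls the first prospective study of stimulants for LOC-E in youth. A pre-treatment rating that was not taken cannot be recovered once the stimulant has started.

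**Working it through.** The plan states no figure on this point, so there is none to reproduce. The check is first a comparison of the text and then an illustration on stated assumptions.

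**Step 1: what is rated when.**

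| Item | Before the stimulant | At 3 months | Planned analysis |
|---|---|---|---|
| LOC-E episodes (ChEDE) | yes | yes | effect size, baseline to 3 months |
| ChEDE-Q8, CEBQ, VADPRS, BIS/BAS, RCADS-25 | yes | yes | effect size, baseline to 3 months |
| Comorbid diagnoses, past and current treatments | yes | not stated | descriptive |
| Adapted side-effects scale | not named | yes | descriptive only |

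**Step 2: what the other baseline scales cover.** The RCADS-25 rates anxiety and depression. The VADPRS adds oppositional, conduct and anxiety/depression subscales. The CEBQ covers eating behavior, including satiety responsiveness, food responsiveness and emotional undereating. Mood, anxiety and appetite therefore have some pre-treatment measurement, though on different instruments that do not allow an item-by-item comparison. As the article describes them, none covers sleep or general physical complaints. A diagnosis reported by the parent is not a symptom rating. That the adapted scale asks about sleep and physical complaints is an assumption, since its content is not shown.

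**Step 3: two possible forms of the items.**
- If they ask whether a complaint is present, pre-existing complaints are counted.
- If they ask about change since starting, the answer depends on recalling the pre-treatment state about 3 months later. The Discussion itself lists recall bias as a limitation, particularly at this age.

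**Step 4: illustration for the first form.** The planned sample of 40 comes from the Participants section. Everything else is assumed: a proportion p0 with the complaint before treatment, presence-only items, every prior complaint persisting to 3 months, and all 40 children rated.

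Children counted with a pre-existing complaint = 40 × p0:
- p0 = 0.10: 40 × 0.10 = 4
- p0 = 0.20: 40 × 0.20 = 8
- p0 = 0.40: 40 × 0.40 = 16

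For the share of reported events, a further assumption is needed: that 30% of children without the complaint develop it. Prevalence at 3 months = p0 + (1 − p0) × 0.30, and the pre-existing share = p0 / prevalence:
- p0 = 0.10: 0.10 + 0.90 × 0.30 = 0.37; share 0.10 / 0.37 = 27%
- p0 = 0.20: 0.20 + 0.80 × 0.30 = 0.44; share 0.20 / 0.44 = 45%
- p0 = 0.40: 0.40 + 0.60 × 0.30 = 0.58; share 0.40 / 0.58 = 69%

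The counts are upper limits for each p0. If only half of the prior complaints persisted, 4 to 16 would become 2 to 8. Fewer children rated would lower the counts in proportion.

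**The case against.** The strongest reply is that the harm is not shown to occur. The scale is adapted and its wording is not given, and adverse events are grouped with information about the treatment. That fits a form asking about problems since starting the drug. This stands as a limit on the claim but does not remove it, because such a form depends on recall and a baseline rating would not.

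Second, the schedule of assessments is in Fig. 1, which is not available here. Its legend names no side-effects scale, but it also omits the scale for the 3-month visit, where the text says it is used, so its silence proves little. It is right to say that no pre-stimulant rating is named; it would be too firm to say that none is taken.

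Third, the RCADS-25, VADPRS and CEBQ already give baseline information on mood, anxiety and eating. This largely answers any worry that appetite suppression goes unmeasured, and it leaves mainly sleep and physical complaints.

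Fourth, adverse events are neither the primary nor a listed secondary outcome, and monitoring them is left to the general practitioner. This limits the importance of the point. They are nevertheless a result the article plans to report.

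A reader might go further and infer that prior complaints will be reported as stimulant adverse events and that the frequencies will be overstated. The documents do not support that. The item wording is unknown, and a single late rating can also miss early complaints that have resolved, so the net direction of error is not established.

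**Conclusion.** The point holds in a limited form. The article places the side-effects rating at 3 months only, names no rating before the stimulant, and plans no comparison with baseline. In an uncontrolled series the 3-month ratings may therefore mix prior complaints with new ones, or rest on recall over about 3 months. The exposure is greatest for complaints that the RCADS-25, VADPRS and CEBQ do not measure.

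The figure of up to 4 to 16 children per complaint is an illustration, not an estimate. It depends on an assumed prior prevalence of 10% to 40%, presence-only items, full persistence and all 40 children being rated. The primary and secondary efficacy analyses are not touched. The change is worth making because it is cheap and the missing information cannot be obtained later.

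**What to change.** Give the same adapted side-effects scale at the existing baseline visit, before the stimulant starts, and report each item as new or worsened since baseline alongside its 3-month frequency.

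State also that adverse-event reporting covers all children who started the stimulant and have a rating, including those who stopped. The Data analytic plan limits the analysis of clinical outcomes to youth who stay on a stimulant for the 3 months, and does not say whether that limit applies to adverse events.

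The cost is a few more minutes of questionnaire time for families at a visit already planned. No extra visits, staff or participants are needed.
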